### 3.3 EXPECTED NUMBER OF PATIENTS

The number of patients expected to enroll would be 3-34 (dependent on dose level obtained and whether an MTD will be tested).

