**4. PROTOCOL COORDINATION, FUNDING, PHASE, MODE, TYPE ETC.**
**Protocol Coordinated By:**

 DF/HCC Investigator [name],  
 MPH

**Funding/Support** (check all that apply):

☒ Industry: AstraZeneca

☐ Federal Organization:

Grant #:

☐ Internal Funding:

☐ Non-Federal:

☐ Other:

**Phase:** Phase 1

**Multi-Center** (i.e., non-DF/HCC site participation):

No

**Cancer Related:** Yes If yes:

Primary Disease Program:

Gastrointestinal Malignancies

or

Primary Discipline Based Program:

Chemoprevention

**Protocol Type:** Therapeutic

If Ancillary, provide parent protocol #:

**Protocol Involves** (check all that apply as listed in the protocol document, even if not part of the research but is mandated by the protocol document):

☐ Chemotherapy

☐ Immunotherapy

☐ Surgery

☐ Bone Marrow/Stem Cell Transplant

☐ Cell Based Therapy

☐ Gene Transfer (use of recombinant DNA)

☐ Radiation Therapy

☐ Hormone Therapy

☐ Vaccine

☒ Data Repository

☐ Exercise/Physical Therapy

☐ Genetic Studies

☐ Human Material Banking

☒ Human Material Collection

☒ Medical Record Review

☐ Questionnaires/Surveys/Interviews

☒ Radiological Exams

☐ Required Biopsy Study

☐ Human Embryonic Stem Cell

☒ Other: patient diaries

**5. SUBJECT POPULATION** (also applies to medical record review and specimen collection studies)

**Total Study-Wide Enrollment Goal:** 34

**Greater than 25% of the overall study accrual will be at DF/HCC:** ☒ Yes ☐ No

**Total DF/HCC Estimated Enrollment Goal:** 34

**Adult Age Range:** 18+

**Pediatric Age Range:** NA

**Will all subjects be recruited from pediatric clinics?** ☐ Yes ☒ No

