## 3 STUDY SPECIFICATIONS

### 3.1 STUDY DESIGN

This is a Phase 1 trial in patients with previously treated stage IV colorectal cancer. The goal is to determine the maximum tolerated dose of ZD6474 with cetuximab and then the maximum tolerated dose of ZD6474, cetuximab and irinotecan.

During the dose finding phase, patients will be enrolled in cohorts of 3. All patients will receive standard doses of cetuximab (400 mg/m^2 loading followed by weekly 250 mg/m^2). Dose levels will be defined as such:

| Dose levels | ZD6474
(daily) | Irinotecan
(q2 wks) | Cetuximab †
(weekly) |
|-------------|-------------------|------------------------|-------------------------|
| 1           | 100 mg            | --                     | 250 mg/m    |
| 2           | 100 mg            | 180 mg/m   | 250 mg/m    |
| 3           | 200 mg            | 180 mg/m   | 250 mg/m    |
| 4           | 300 mg            | 180 mg/m   | 250 mg/m    |

† - after 400 mg/m^2 loading dose

The study will initially enroll into dose level 1. If 0 of 3 patients have a dose limiting toxicity (DLT) then we will advance to dose level 2. If 1 of 3 patients have a DLT, then 3 additional patients will be treated at dose level 1. If 2 patients have a DLT at

dose level 1, the study will close. If <33% of patients have a DLT at dose level 1, we will proceed to dose level 2.

At dose levels 2, we will initiate treatment with irinotecan. Treatment at dose levels 2-4 will begin with 2 weeks of only ZD6474 and Cetuximab. Irinotecan will begin on day 15 (week 3). If 0 of 3 patients have a DLT, we will proceed to the next dose level. If 1 of 3 patients have a DLT, then 3 additional patients will be treated at the same dose level. If 2 patients have a DLT, then the MTD will be current dose level -1 (if on dose level 1, study closes). If < 33% of patients have a DLT, then the study will continue to the next dose level (if at level 4, the MTD for ZD6474 will be considered 300 mg).

Cycles of therapy will be defined as 4 weeks on therapy, even if drugs are held for a portion of that time.

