### 3.2 DOSE LIMITING TOXICITIES

DLTs (defined as within the first 28 days of treatment in dose level 1 and first 35 days in dose levels 2-4) will include: grade IV hematological toxicity > 7 days; fever and neutropenia; grade III diarrhea leading to hospitalization or lasting > 48 hours despite aggressive anti-diarrheal medication; grade IV diarrhea despite aggressive anti-diarrheal medication; grade IV vomiting despite optimal antiemetics; or grade III or higher nonhematological toxicity (excluding nausea, vomiting, diarrhea, or alopecia) lasting > 1 week; grade 4 skin toxicity; grade 3 or greater cardiac toxicities; or death.

If patients in dose levels 2-4 who have a DLT in the first 14 days (prior to initiation of irinotecan), the patient will not be counted towards the DLTs of that cohort and an additional patient will be substituted. For example, if one of the first 3 patients in dose level 2 have a DLT, that patient will not be calculated into the DLT tabulation for ZD6474, cetuximab and irinotecan and an additional patient will be substitute in that spot. If this scenario occurs twice, the study will be held and the study team will reevaluate the ZD6474 / cetuximab toxicities.

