### 13 Statistical Considerations

This is a phase I study, initially with dose escalation of ZD6474 and then adding irinotecan. The study will likely accrue between 6 and 15 patients (before MTD testing) with the described dose escalation schema, though it could range from 3 to 34 patients. We expect accrual to be 2-3 patients / month (though this will vary during waiting periods to proceed to next dose level). If patients in dose levels 2-4 who have a DLT in the first 14 days (prior to initiation of irinotecan), the patient will not be counted towards the DLTs of that cohort and an additional patient will be substituted. For example, if one of the first 3 patients in dose level 4 have a DLT, that patient will not be calculated into the DLT tabulation for ZD6474,

cetuximab and irinotecan and an additional patient will be substitute in that spot. If this scenario occurs twice, the study will be held and the study team will reevaluate the ZD6474 / cetuximab toxicity profile. To ensure the toxicity at the MTD is acceptable and to further define any toxicity that may occur with this regimen, an additional 10 patients will be accrued at the MTD. The estimation of toxicity rate will be based on these 10 additional patients. With 10 patients, the 90% confidence bounds for any toxicity will be  $\pm 28\%$ . The probability of a dose level declared too toxic based on the true DLT rate is defined as such:

| True DLT Rate | Probability of declaring dose too toxic |
|---------------|-----------------------------------------|
| 20%           | 0.29                                    |
| 30%           | 0.51                                    |
| 40%           | 0.69                                    |
| 50%           | 0.83                                    |
| 60%           | 0.92                                    |

Response rate, progression-free survival and overall survival are secondary analyses. Each will be reported by dose level and at the MTD.

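### The stated maximum of 34 patients counts only the 24 escalation places and the 10 at the MTD, and leaves out the substitutes that the protocol itself requires

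*Protocol*

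**What the plan says.** - **Section 3.3** gives the range, "The number of patients expected to enroll would be 3-34", and ties it to the dose level reached and to whether an MTD is tested. Substitution is not among the things it depends on.
- **Section 13** expects a smaller number before MTD testing, then gives the outer limits: "though it could range from 3 to 34 patients". The same paragraph restates the substitution rule and adds 10 patients at the MTD.
- **The synopsis** repeats 3-34 as the total expected number. **The front sheet** (Subject Population) has "Total Study-Wide Enrollment Goal: 34".
- **Section 3.1** sets four dose levels: "During the dose finding phase, patients will be enrolled in cohorts of 3". Three more patients are treated at a level if 1 of the first 3 has a DLT. For the irinotecan levels, "Treatment at dose levels 2-4 will begin with 2 weeks of only ZD6474 and Cetuximab".
- **Section 3.2**, repeated in sections 7 and 13, covers a patient at levels 2-4 whose DLT falls in those first 14 days: "the patient will not be counted towards the DLTs of that cohort and an additional patient will be substituted". If this happens twice, the study is held and the team re-evaluates the toxicity of ZD6474 with cetuximab.

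**The concern.** A patient replaced under section 3.2 has been registered and treated. Section 11 puts everyone who receives one dose into any safety analysis. Such a patient therefore adds to enrollment but fills no cohort place. If 34 is already the sum of all cohort places plus the MTD patients, a single required substitution on the fullest path takes the trial past its own stated maximum.

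The figure at stake is the stated upper limit on patients exposed, which also appears as the enrollment goal on the front sheet. The MTD patients are accrued last, and section 13 bases the toxicity estimate on those 10. If 34 were ever applied as a strict cap on such a path, the shortfall would fall on them.

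**Working it through.** **Inputs.** Four dose levels; 3 patients per level, plus 3 if 1 of 3 has a DLT (section 3.1); 10 further patients at the MTD (section 13); one substitute for each DLT in days 1-14 at levels 2-4 (section 3.2); a hold at the second occurrence (section 3.2).

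**Step 1: confirm at most 6 counted patients per level.** Under the section 3.1 rule, the probability that a level is declared too toxic at true DLT rate p is 1 - [(1-p)^3 + 3p(1-p)^2 x (1-p)^3].

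| p | Computed | Section 13 |
|---|---|---|
| 20% | 0.291 | 0.29 |
| 30% | 0.506 | 0.51 |
| 40% | 0.691 | 0.69 |
| 50% | 0.828 | 0.83 |
| 60% | 0.918 | 0.92 |

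The table reproduces, so the design uses 3 or 6 counted patients per level.

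**Step 2: reproduce the stated range.** Enumerating every path without substitution gives 3 to 24 patients in escalation.
- Minimum total: 3 (the study closes at level 1).
- Maximum total: 4 x 6 + 10 = 34.

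Both ends match the protocol, and every place on the maximum path is taken.

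**Step 3: add the required substitutes.** The protocol does not say whether the two occurrences are counted per cohort or across the study, or whether accrual can resume after a hold.

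| Reading | Substitutes | Maximum |
|---|---|---|
| Study-wide, before any hold | 1 | 34 + 1 = 35 |
| Study-wide, second patient also replaced, accrual resumes | 2 | 34 + 2 = 36 |
| Per cohort, one at each of levels 2-4, no hold | 3 | 34 + 3 = 37 |
| Per cohort, two at each of levels 2-4, accrual resumes each time | 6 | 34 + 6 = 40 |

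**Step 4: how likely is it?** If one level stays at 3, the base is 3 x 6 + 3 + 10 = 31, and three substitutes only bring it to 34. So with up to three substitutes, exceeding 34 needs all four levels to expand. Levels 1-3 must each have 1 DLT in the first 3 and none in the next 3; level 4 must have 1 in the first 3, whatever follows. For a common DLT rate p (assumed):

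P = [3p(1-p)^2 x (1-p)^3]^3 x 3p(1-p)^2

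- p = 10%: 0.177^3 x 0.243 = 0.0014
- p = 20%: 0.197^3 x 0.384 = 0.0029
- p = 30%: 0.151^3 x 0.441 = 0.0015

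Letting the rate differ by level, the most this can reach is 0.201^3 x 0.444 = 0.0036.

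**Step 5: an early DLT is needed as well.** With 18 counted places at levels 2-4 and assumed early-DLT rates of 2%, 5% and 10%, the chance of at least one substitution is 1 - (1 - rate)^18 = 0.31, 0.60 and 0.85. Multiplying the lowest values (0.0014 x 0.31) and the highest (0.0029 x 0.85) gives roughly 0.04% to 0.25% for exceeding 34. The protocol gives no early-DLT rate, so this range rests on assumption.

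**The case against.** The best defence is that 34 is a planning figure. Section 3.3 and the synopsis use the language of expectation, and the front sheet calls it a goal. On nearly every path some level does not expand, so substitutes fit within 34. Section 14.6 allows an IRB-approved amendment if more places were needed. Nothing inferential rests on the number: the escalation rule, the MTD definition, the toxicity table and the 10-patient estimate are the same with or without it.

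Most of this stands, and it limits the importance of the point. It does not remove the inconsistency. Section 13 describes what accrual could range over, which is a limit, in the same paragraph as the rule that breaks it. No section makes an allowance for substitutes.

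Three stronger readings are tempting, and the protocol does not support them:

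- **That the correct range is 3-37.** This needs the two occurrences to be counted per cohort, which the text does not say. It says the study is held, which fits a study-wide count at least as well. The first firm figure above 34 is 35.
- **That 34 can only be exceeded if every level expands.** This holds for up to three substitutes. If accrual resumed after a hold and a fourth were enrolled, three expanded levels would be enough: 31 + 4 = 35.
- **That 34 was a binding limit which shortened the MTD cohort.** The revision log records closure in May 2010 because the target enrollment goal was met. It gives no count, mentions no substitutes and shows no shortfall at the MTD.

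**Conclusion.** The point holds as a minor error in a stated limit. The figure of 34 is exactly the maximum without substitution, while the protocol makes substitution mandatory, so the true maximum is at least 35. The text cannot fix it more closely, because neither the scope of the two-occurrence rule nor resumption after a hold is defined.

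The error is in the ceiling. Likely enrollment and the toxicity table are unaffected, and exceeding 34 with up to three substitutes has a probability well under 1%. That probability assumes a common DLT rate of 10-30% among counted patients (or at most 0.36% for full expansion with any mix of rates). The maxima in the working assume that substitution applies to the escalation cohorts only.

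**What to change.** If the substitution rule is kept:

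1. State 34 as the maximum before substitutions, with its derivation (4 x 6 + 10), and say that substitutes are additional.
2. In sections 3.2, 7 and 13, state whether the two occurrences are counted per cohort or across the study, whether the second patient is also replaced, and whether accrual can resume after a hold. Which of these applies is for the study team to decide.
3. Carry the single maximum that follows, at least 35, to the front sheet, the synopsis, section 3.3 and section 13.

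If the rule were removed, 34 would be correct as it stands. The cost is a restated figure in four places and a clarifying sentence where the rule appears. Expected enrollment, the escalation scheme and the section 13 table do not change.

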### 3.4 METHOD OF TREATMENT ALLOCATION

A patient number will be assigned by the Quality Assurance Office for Clinical Trials (QACT) to each patient upon registration. The overall study coordinator (based at DFCI) will assign the dose level.

### 3.5 DURATION OF THERAPY

Patients will continue the study treatment until disease progression, unacceptable toxicity, or development of any of the criteria for patient discontinuation as described in Section 11 of the protocol.

Patients will be considered to be on-study for the duration of their treatment and during the 30 days following treatment discontinuation. Treatment discontinuation is defined as the last day of study treatment.

All included patients will be followed up until recovery or stabilization of all adverse events or return to baseline condition.

## 4 STUDY POPULATION

### 4.1 INCLUSION CRITERIA

Patients must meet all of the following criteria in order to be eligible for entry into the trial:

- (1) Eligible patients must have histologically or cytologically documented locally advanced or metastatic colorectal cancer
- (2) 1-2 prior therapies for metastatic colorectal cancer. Prior adjuvant therapy not included in the number of priors unless recurrence within 12 months of last dose of therapy and then the adjuvant therapy will be counted as 1 prior.
- (3) Patients must have measurable disease according to the RECIST criteria.
- (4) Tumor is K-ras wildtype by method of choice at respective institution (testing codons 12 and 13). Since testing for K-ras should be standard of care for use of cetuximab in metastatic colorectal cancer, testing can be performed prior to signing consent or after consent but prior to enrollment.
- (5) Age > 18 years
- (6) ECOG Performance Score of 0-2.
- (7) Patients should have completed any major surgery 4 weeks from registration. Patients must have completed any minor surgery 2 weeks from registration. Patients must have fully recovered from the procedure and have completely healed surgical incisions before starting therapy.. (Insertion of a vascular access device is not considered major or minor surgery.)
- (8) Adequate bone marrow as evidenced by:
  - Absolute neutrophil count  $\geq 1,200/\text{mL}$
  - Platelet count  $\geq 100,000/\text{mL}$
- (9) Adequate renal function as evidenced by serum creatinine  $\leq 1.5 \times \text{ULRR}$  or creatinine clearance  $\geq 50 \text{ mL/minute}$  (calculated by Cockcroft-Gault formula)
- (10) Adequate hepatic function as evidenced by:
  - Serum total bilirubin  $\leq 1.5 \text{ mg/dL}$
  - Alkaline phosphatase  $< 3\text{X}$  the ULN for the reference lab ( $< 5\text{X}$  the ULN for patients with known hepatic metastases)
  - SGOT/SGPT  $< 3\text{X}$  the ULN for the reference lab ( $< 5\text{X}$  the ULN for patients with known hepatic metastases)
- (11) Normal range of serum calcium (ionized or adjusted for albumin) and magnesium (supplementation permitted)
- (12) Patients or their legal representatives must be able to read, understand and provide informed consent to participate in the trial.
- (13) Patients of childbearing potential and their partners must agree to use an effective form of contraception during the study and for 90 days following the last dose of study medication (an effective form of contraception is an oral contraceptive or a double barrier method)
- (14) For women who have not had a hysterectomy and under 60 years of age, a negative urine or serum pregnancy test. Male patients must be surgically

sterile or using an acceptable method of contraception during their participation in this study

#### 4.2 EXCLUSION CRITERIA

Patients meeting any of the following criteria are ineligible for study entry:

- (1) History of prior malignancy within the past 3 years except for curatively treated basal cell carcinoma of the skin, cervical intra-epithelial neoplasia, or treated localized prostate cancer with a current PSA of  $< 1.0$  mg/dL on 2 successive evaluations, at least 3 months apart, with the most recent evaluation no more than 4 weeks prior to entry.
- (2) Prior therapy with gefitinib, erlotinib, cetuximab, ABX-EGF or other specific EGFR inhibitor. Note that prior therapy with either bevacizumab and/or irinotecan is NOT an exclusion criteria
- (3) Patients with known hypersensitivity to any of the components of cetuximab or ZD6474 or irinotecan
- (4) Patients who are pregnant or lactating
- (5) Any other medical condition, including mental illness or substance abuse, deemed by the clinician to be likely to interfere with a patient's ability to sign informed consent, cooperate and participate in the study, or interfere with the interpretation of the results.
- (6) Potassium  $< 4.0$  mEq/L despite supplementation;
- (7) Serum calcium (ionized or adjusted for albumin,) or magnesium out of normal range despite supplementation.
- (8) Evidence of severe or uncontrolled systemic disease or any concurrent condition which in the Investigator's opinion makes it undesirable for the patient to participate in the trial or which would jeopardize compliance with the protocol.
- (9) Clinically significant cardiac event such as myocardial infarction; New York Heart Association (NYHA) classification of heart disease  $\geq 2$  that, in the opinion of the Investigator, increases the risk of ventricular arrhythmia (see Appendix B) within 3 months before entry; or presence of cardiac disease
- (10) History of arrhythmia (multifocal premature ventricular contractions (PVCs), bigeminy, trigeminy, ventricular tachycardia, or uncontrolled atrial fibrillation) which is symptomatic or requires treatment (CTCAE grade 3) or asymptomatic sustained ventricular tachycardia. Atrial fibrillation, controlled on medication is not excluded.
- (11) Previous history of QTc prolongation as a result from other medication that required discontinuation of that medication.
- (12) Congenital long QT syndrome, or 1st degree relative with unexplained sudden death under 40 years of age.
- (13) Presence of left bundle branch block (LBBB.)
- (14) QTc with Bazett's correction that is unmeasurable, or  $\geq 480$  msec on screening ECG. If a patient has QTc  $\geq 480$  msec on screening ECG, the screen ECG may be repeated twice. The average QTc from the three screening ECGs must be  $< 480$  msec in order for the patient to be eligible for the study.) Patients who are receiving a drug that has a risk of inducing

Torsades de Pointes are excluded if QTc is  $\geq 460$  msec (see Appendix A, Drug List 1; section 5.2)

- (15) Any concomitant medication that are potent inducers of CYP3A4 (rifampicin, rifabutin, phenytoin, carbamazepine, Phenobarbital, St. John's Wort) For a comprehensive list of medications which may affect activity of CYP3A4, please visit:

<http://www.medicine.iupui.edu/clinpharm/ddis/ClinicalTable.asp> and  
<http://www.pharmacytimes.com/issue/pharmacy/2008/2008-09/2008-09-8687>.

- (16) Hypertension not controlled by medical therapy (systolic blood pressure greater than 160 mm Hg or diastolic blood pressure greater than 100 mm Hg)
- (17) Patients lacking physical integrity of the upper gastrointestinal tract or who have malabsorption syndrome.
- (18) Currently active diarrhea that may affect patient's ability to absorb ZD6474 or tolerate potential diarrhea from study drugs.
- (19) Receipt of any investigational agents within 30 days prior to commencing study treatment
- (20) Last dose of prior chemotherapy or radiation therapy discontinued less than 4 weeks before the start of study therapy
- (21) Incompletely healed surgical incisions, at the discretion of the investigator.
- (22) Any unresolved toxicity greater than CTC grade 1 from previous anti-cancer therapy
- (23) EGFR by immunohistochemistry will NOT be an exclusion

#### 4.3 RESTRICTIONS

- (1) Due to the experimental nature of ZD6474, female patients must be 1 year post-menopausal, surgically sterile or using acceptable method of contraception. Male patients must be surgically sterile or using an acceptable method of contraception during their participations in this study and for 3 months after discontinuation of study drug.

## 5 STUDY PROCEDURES

### 5.1 TREATMENT REGIMEN

Treatment will be administered on an outpatient basis. Expected adverse events and appropriate dose modifications for study drugs are described in Section 6 and 7. No investigational or commercial agents or therapies other than those described below may be administered with the intent to treat the patient's malignancy.

This is a phase I study. Entry into dose levels are described in section 3. Initiation of ZD6474 will occur on the first day of treatment in the clinic or infusion unit. The patient will take the first dose of medication in the presence of the treating clinician or nurse. Thereafter, ZD6474 will be self-administered around the same time daily. If the patient inadvertently does not take the dose at their usual time, or has emesis within 30 minutes of taking ZD6474 tablet, the patient may take that dose any time

within 6 hours of the same day. The daily treatment schedule will be resumed the next day with the patient taking the scheduled dose at their usual time.

Cetuximab will be initiated on the first day of treatment at all dose levels. For the first treatment, ZD6474 should be given first and then at least 30 minutes should elapse prior to start of infusion of cetuximab. For the first treatment, patients will be premedicated with 50 mg IV of diphenhydramine 30-60 minutes prior to receiving 400mg/m^2 IV of Cetuximab over 120 minutes. Subsequently doses will be weekly infusions of 250 mg/m^2 IV over 60 minutes. The infusion rate of cetuximab must never exceed 10 mg/minute (5 mL/min). Premedication with diphenhydramine may be administered prior to subsequent doses, but at the Investigator's discretion, the dose of diphenhydramine (or similar agent) may be reduced.

In dose levels 2-4 and at the MTD (if includes irinotecan), irinotecan will be initiated on day 15 after administration of cetuximab. Irinotecan will be an IV infusion over 90 minutes every other week.

